In order to implement research to improve patients' visiting behavior to physicians after CKD screening in the general population, we launched the pragmatic trial of nudging CKD patients after screening. The trial was designed in the Japanese health care system, which has features of a universal health care system and large-scale CKD screening. The aim of the trial is to evaluate whether a behavioral intervention (i.e., a usual letter and nudge-based letter) would improve CKD patients’ visiting behaviors to physicians and protect their kidney function.

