### Outcomes

2.5

Our primary outcome is proportion of patients’ visiting physicians for 6 months after the intervention, and the secondary outcome is the change in the eGFR at 2 years after the intervention (Table 1). The primary outcomes of visiting physicians after the intervention is defined independently of the presence or absence of the visit before the intervention. Although our definition of visiting physicians after the intervention may include the follow-up visit (re-visit after the intervention with a history of visiting physicians before the intervention), this does not affect internal validity of the trial. Follow-up of participants will end at 2 years after their intervention data are collected or until they leave the HIA^2^CE.

**Table 1 tbl1:** Outcomes.

Primary outcome
**Proportion of visiting** The proportion of participants who visit physicians for CKD care for 6 months after the intervention

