#### Sample size

2.6.1

Based on past medical claims data and results from the previous intervention, we assume that the proportions of patients visiting physicians in each group are 0.15, 0.20, and 0.25 in the control group, usual letter group, and nudge-based letter group, respectively. We set the allocation ratio as 1:2:2 for the control group, usual letter group, and nudge-based letter group, respectively. The sample sizes of 850, 1700, and 1700 patients for each group were determined to achieve ≥80% power overall and for all pairwise comparisons with the chi-square test by the simulation-based approach. The sample size provides ≥99% power to detect the difference of change from the baseline eGFR of −3 (standard deviation = 10) with a two-sided significance level of 0.05.

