#### Data analysis

2.6.2

We will describe participant characteristics with means and proportions by groups and compare them between groups using analysis of variance and chi-square tests, and their non-parametric analogs, as appropriate.

In our analysis to evaluate the effect of the intervention, we will conduct an intention-to-treat analysis. In our primary analysis, we will apply a logistic regression model with a dichotomous variable of visiting behavior as the dependent variable, and dummy variables of three groups and allocation adjustment factors (quarterly timing of the intervention, eGFR, and urine protein) as the independent variables. In the logistic regression model, we will estimate p-values by omnibus tests (Wald test) for the differences in outcome (proportion of visits to physicians) between the groups. If the two-sided p-values by omnibus tests is <5%, we will conclude that there are statistically significant differences in outcome between the groups and will continue to perform pairwise comparisons in order to adjust for multiple comparisons [18]. From the logistic regression model, we will estimate risk differences and their 95% confidence intervals using the model-based standardization technique [19]. In a sensitivity analysis, we will adjust for the presence of lifestyle guidance involved in the usual follow-up after the health checkup. We will also estimate the proportion and its Wald-type 95% confidence interval of the primary outcome for each group. Further, we will estimate the odds ratio and its 95% confidence intervals, and compare them between the groups.

For the confirmatory analysis of the secondary outcome, we will apply the closed testing procedure. Specifically, only if the two-sided p-values by the omnibus test of the primary outcome are <5%, we will conduct the following analysis on the difference of the eGFR. We will apply a linear regression model with the difference of the eGFR as the dependent variable, and dummy variables of the three groups and allocation adjustment factors (quarterly timing of the intervention, eGFR, and urine protein) as the independent variables. We will estimate p-values by omnibus tests (Wald test) to determine differences in outcome (i.e., the difference of eGFR) between the groups. If the two-sided p-values by omnibus tests are <5%, we will conclude that there are statistically significant differences in outcome between the groups and will continue to conduct pairwise comparisons.

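### Section 2.6.2 makes running the 2-year eGFR model, and comparing arms on it, conditional on significance, and specifies no eGFR estimate outside those gates

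*Protocol article*

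**What the plan says.** The Introduction of the protocol article gives the aim as finding out whether the letters "would improve CKD patients’ visiting behaviors to physicians and protect their kidney function". Section 2.5 (Outcomes) states that "the secondary outcome is the change in the eGFR at 2 years after the intervention". Section 2.1 and the Fig. 1 legend say, without any condition, that the groups will be compared on visiting and on change in kidney function.

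Section 2.6.2 sets out the eGFR analysis in four steps:

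1. Scope: "For the confirmatory analysis of the secondary outcome, we will apply the closed testing procedure".
2. First gate: "only if the two-sided p-values by the omnibus test of the primary outcome are <5%, we will conduct the following analysis on the difference" of eGFR. The analysis that follows is a linear regression of eGFR change on group indicators and the allocation factors.
3. Named output: "We will estimate p-values by omnibus tests (Wald test) to determine differences in outcome (i.e., the difference of eGFR) between the groups".
4. Second gate: "If the two-sided p-values by omnibus tests are <5%, we will conclude that there are statistically significant differences in outcome between the groups", after which pairwise comparisons are made.

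For visiting, the same section also makes pairwise comparisons depend on an omnibus test. It separately promises, with no condition attached, that "we will estimate risk differences and their 95% confidence intervals using the model-based standardization technique", together with group proportions and odds ratios with intervals. The eGFR paragraphs contain no equivalent sentence.

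**The concern.** Hierarchical testing controls error by limiting which significance claims count as confirmatory. Error control does not require that a model go unfitted or an estimate be withheld. Here the condition is attached to conducting the regression, and a second condition to comparing the arms.

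On the literal rule there are three possible results for eGFR: no analysis, an omnibus test with no arm contrasts, or arm contrasts after both gates have opened. In the first two cases the trial would not report how large or small the kidney effect could be, although that is half of its stated aim. The lost information would be precise. An eGFR estimate added after a failed gate would also be post hoc against the published text, which weakens it for no good reason.

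**Working it through.** Inputs, all from section 2.6.1 (Sample size) unless marked as assumptions: 850 control, 1700 usual letter, 1700 nudge-based letter; visiting proportions that "are 0.15, 0.20, and 0.25 in the control group, usual letter group, and nudge-based letter group, respectively"; eGFR difference of 3 in absolute value; SD 10; two-sided alpha 0.05. Section 2.5 allows follow-up to end when a participant leaves the insurer but gives no attrition rate, so 0% to 40% loss of 2-year eGFR is used as an assumed range.

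**1. The plan's own power figures.**
- 0.15 v 0.20 (850 v 1700): pooled proportion (127.5 + 340)/2550 = 0.1833. Null SE = √[0.1833 × 0.8167 × (1/850 + 1/1700)] = 0.01626. Alternative SE = √(0.15 × 0.85/850 + 0.20 × 0.80/1700) = 0.01562. z = (0.05 − 1.96 × 0.01626)/0.01562 = 1.16, so power is 87.7%.
- The same formula gives 93.7% for 0.20 v 0.25 and over 99.9% for 0.15 v 0.25.
- In 200,000 simulated trials the omnibus test had over 99.9% power, and the omnibus test plus all three pairs jointly had 81.5%.
- eGFR, letter v control: SE = 10 × √(1/850 + 1/1700) = 0.420; 3/0.420 − 1.96 = 5.18, so power exceeds 99.9%.

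The stated 80% and 99% therefore reproduce.

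**2. Precision available for eGFR.** Half-width = 1.96 × SD × √(1/n₁ + 1/n₂).
- Letter v control: 1.96 × 10 × √(1/850 + 1/1700) = 0.82.
- Nudge v usual: 1.96 × 10 × √(2/1700) = 0.67.
- Loss in every arm divides these by √(1 − loss). At 20% loss they are 0.92 and 0.75; at 40% loss, 1.06 and 0.87.

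**3. What a null eGFR omnibus test would imply.** The omnibus Wald statistic has 2 degrees of freedom and a 5% critical value of 5.99. With a common variance, no pairwise Wald statistic can exceed the omnibus one. A non-significant omnibus test therefore limits each difference to √5.99 = 2.45 standard errors. For a letter v control that is 2.45 × 0.420 = 1.03, and the far end of the 95% interval is at most 1.03 + 0.82 = 1.85. At 40% loss the SE is 0.420/√0.6 = 0.542, and the limit is 2.45 × 0.542 + 1.06 = 2.39. In both cases the interval excludes 3.

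**4. How often each gate would stay closed.** Only the first line of the first list uses the plan's own effects; the other effects are illustrative assumptions.

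First gate (visiting omnibus not significant), simulated:
- 0.15/0.20/0.25: under 0.01%
- 0.15/0.175/0.20: 18%
- 0.15/0.165/0.18: 60%
- 0.15/0.16/0.17: 80%
- no letter effect: 95%

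Second gate (eGFR omnibus not significant), noncentral chi-square with noncentrality Σnᵢ(μᵢ − μ̄)²/SD²:
- Differences from control of 0/0.5/1.0: μ̄ = 2550/4250 = 0.6; noncentrality = (850 × 0.36 + 1700 × 0.01 + 1700 × 0.16)/100 = 5.95; gate closed 42% of the time.
- 0/0.25/0.5: 82%.
- No difference: 95%.

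**The case against.** The strongest reply is that the gate sits under a sentence about confirmatory analysis, so it may govern only confirmatory inference, which is close to what is asked for here. Section 2.1 and the Fig. 1 legend also announce an eGFR comparison with no condition, and an ungated descriptive estimate is nowhere forbidden. This stands in part: the text does not say that eGFR will go unreported. But section 2.1 and the legend state only a general intent and name no estimate, while section 2.6.2, where the method is fixed, states when the analysis is to be conducted.

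A reader might infer more than the document supports in three ways.

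- That the eGFR analysis yields p-values only. The group coefficients of the stated linear model are adjusted mean differences, and the standard errors behind the Wald test give the intervals. A condensed article that does not name an interval for a secondary outcome may be leaving that to the full protocol or analysis plan.
- That reporting after a significance filter would overstate the effect. At the design difference of 3, power exceeds 99.9%, so almost nothing is filtered out and any such bias would be negligible.
- That the gatekeeping is itself wrong. Testing the primary before the secondary outcome, and an omnibus test before three pairwise tests, is ordinary multiplicity control.

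It is also fair to say that, under the plan's visiting assumptions, the first gate would almost never close. That does not protect against weaker letters, and it has no bearing on the second gate, which can stay closed after a fully successful primary result.

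**Conclusion.** The point holds as a fault of wording with a real consequence. Section 2.6.2 ties both the running of the 2-year eGFR model and the comparison of arms to significance, and the article specifies no eGFR estimate outside those conditions. Followed literally, a null visiting or eGFR omnibus result would leave unreported intervals of about ±0.82 (letter v control) and ±0.67 (nudge v usual) mL/min/1.73 m². These half-widths rest on the plan's SD of 10 and full follow-up; under the assumed 40% loss they widen to ±1.06 and ±0.87. They ignore any gain from covariate adjustment. The sample size, the power figures and the test order are not in question.

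**What to change.** Add two sentences to section 2.6.2. First, the stated linear model will be fitted, and the three adjusted mean differences in 2-year eGFR change (usual letter v control, nudge v control, nudge v usual) reported with 95% confidence intervals, whatever the omnibus p-values for visiting and for eGFR. Second, the closed testing sequence decides only which significance claims are confirmatory; after a failed gate the same estimates and intervals are presented as descriptive, with no significance claim.

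The cost is the wording. No new data are needed, and sample size, alpha and the order of tests stay as they are. If a full analysis plan already provides for this, the two texts should be aligned.

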### Randomization

2.4

For this pragmatic trial in the health care system, a research coordinator from the health insurance association assigned eligible participants and generated a unique number for each. After stratifying patients by the timing of screening (quarterly), eGFR (≥60 mL/min or <60 mL/min), and urine protein (≥+ or ≤±), we conduct random allocation with the permuted block method for each stratum. We randomize participants in a 2:2:1 ratio into the usual letter group, nudge-based letter group, and control group, respectively.

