**Secondary outcome**
**Change in the eGFR** Change in the eGFR (mL/min/1.73 m^2^) from the pre-intervention value to the post-intervention value after 2 years
**Proportion of continuous visiting** The proportion of participants who visit physicians for CKD care at least twice between 1 year and 2 years after the intervention

CKD, chronic kidney disease; eGFR, estimated glomerular filtration rate.

The medical claims data from the intervention date to 6 months after the intervention is used to define visiting behavior. If the participants have CKD-related diagnostic codes (Table 2) in their medical claims during this period, it is considered that they visited physicians for CKD care. The health checkup data of pre-intervention and post-intervention (2 years later) is used to define change in the eGFR.

**Table 2 tbl2:** Chronic kidney disease-related diagnostic codes.

	ICD-10 codes
Chronic kidney disease	N170, N171, N172, N178, N179, N180, N188, N189, N19, N990
Tubulointerstitial nephritis	N110, N111, N118, N119, N12, N140, N141, N142, N143, N144, N150
Chronic glomerular nephritis	N002, N003, N004, N006, N007, N009, N012, N014, N016, N017, N019, N028, N029, N030, N032, N033, N034, N036, N037, N039, N040, N042, N044, N046, N049, N050, N051, N052, N053, N054, N055, N056, N057, N058, N059, N069, N079, N085
Diabetic nephropathy	E102, E112, E132, E142
Hypertensive nephrosclerosis	I129, I120
Polycystic kidney disease	Q613

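### The 2-year eGFR-change model appears to adjust for baseline eGFR only as below versus at or above 60; adding the measured value would be a free, minor gain in precision

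*Protocol article*

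**What the plan says.** All references are to the protocol article.

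- **Outcome.** Table 1 (section 2.5) defines the secondary outcome as eGFR change "from the pre-intervention value to the post-intervention value after 2 years".
- **Model.** Section 2.6.2 says "We will apply a linear regression model with the difference of the eGFR as the dependent variable". The covariates are dummies for the three groups and "allocation adjustment factors (quarterly timing of the intervention, eGFR, and urine protein) as the independent variables". The article calls this the confirmatory analysis of the secondary outcome and gates it on the omnibus test of the primary outcome.
- **Coding of the eGFR factor.** Section 2.6.2 does not restate it. Section 2.4 defines the stratification factor as "eGFR (≥60 mL/min or <60 mL/min"), that is, two levels. Nothing in the article names the measured baseline eGFR as a covariate.
- **Planning figures.** Section 2.6.1 states: "The sample size provides ≥99% power to detect the difference of change from the baseline eGFR of −3 (standard deviation = 10"). The test there is two-sided at the 5% level, and the group sizes are 850 (control), 1700 (usual letter) and 1700 (nudge-based letter).

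**The concern.** A change score contains the baseline value with a negative sign. Participants enter on one screening reading (acknowledged in section 4), so some regression to the mean is expected: low first readings tend to rise at re-measurement and high ones to fall. Baseline is therefore an expected predictor of change, and a continuous baseline covariate is the usual way to use that.

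A single cut at 60 is coarse here. Eligibility requires eGFR below 60 or urine protein of at least 1+, so no participant can be both at or above 60 and protein-negative. The eGFR and protein factors therefore form only three cells per quarter, and everyone at or above 60 falls in one cell with no upper limit. Variation in baseline within a cell stays in the residual, and a chance difference in baseline between arms within a cell is not corrected. What is at stake is precision for a secondary outcome.

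**Working it through.** **1. The plan's own power figure.**

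Inputs (section 2.6.1): difference 3, SD 10, two-sided α = 0.05, groups 850/1700/1700.

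- Control vs a letter group: SE = 10 × √(1/850 + 1/1700) = 10 × 0.0420 = 0.420. Then 3/0.420 = 7.14 and power = Φ(7.14 − 1.96), above 99.99%.
- Letter vs letter: SE = 10 × √(2/1700) = 0.343, and power is again above 99.99%.

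The stated figure of at least 99% is reproduced. About 307 controls with 614 in a letter group would already give 99%.

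**2. How strongly baseline might predict change.**

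The article gives no correlation, so this step rests on assumptions.

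- Baseline SD: Table 3 gives 15.2, 16.0 and 15.9 (first-quarter enrolment), pooled about 15.8, variance about 250.
- Change SD: 10, taken from section 2.6.1, variance 100.
- Assumption: equal variances at baseline and follow-up.

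Var(change) = 2 × 250 × (1 − r) = 100, so r = 0.80. The slope of change on baseline is r − 1 = −0.20. Baseline as a whole would then explain 0.20² × 250 = 10 of 100 variance units.

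**3. What the two-level term already removes.**

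A simulated population of 1,000,000 was matched to Table 3 (mean 68.5, SD 15.8, 63.4% protein-positive). The shape of its distribution is an assumption. The strata left a within-stratum baseline SD of about 9. At a slope of −0.195 the residual variances were:

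| Model | Residual variance | SE, 850 vs 1700 |
|---|---|---|
| Strata only | 93.6 | √93.6 × 0.0420 = 0.406 |
| Strata + continuous baseline | 90.3 | √90.3 × 0.0420 = 0.399 |

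The further reduction is (93.6 − 90.3)/93.6 = 3.5% from these rounded values (3.6% as reported from the simulation), or about 1.8% in SE. For slopes of −0.10 and −0.30 the reductions are 0.9% and 9.4%, or about 0.5% and 5% in SE.

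A closed form gives a cross-check. With slope b, within-stratum SD w = 9 and total change variance 100, the gain is b²w² / [100 − b²(250 − w²)]. For b = −0.2 this is 3.24/93.2 = 3.5%. For b = −0.1 and −0.3 it is 0.8% and 8.6%.

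A second simulation modelled selection on a single noisy reading (within-person SD 3 to 7, change SD about 10). It gave a smaller gain of 0.1 to 2.6% in SE. Strata plus baseline explained 0.6 to 14.0% of the variance in change, against 0.4 to 9.3% for the strata alone.

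**4. What this does to power, control vs a letter group.**

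- True difference 3: above 99.99% with or without the covariate.
- True difference 2: 99.8% with strata only, 99.9% with baseline added.
- True difference 1: 1/0.406 = 2.46, power Φ(0.50) = 69%; with baseline added 1/0.399 = 2.51, power Φ(0.55) = 71%.

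**5. Chance imbalance.**

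Within strata, the chance SE of the baseline difference between control and a letter group is about 9 × 0.0420 = 0.38 mL/min. At a slope of −0.2 a one-SE imbalance moves the treatment contrast by 0.38 × 0.2 = 0.08 mL/min.

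These figures assume that all 4,250 planned participants have a 2-year value. Losses raise both SEs by the same factor and leave the percentage gain unchanged.

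**The case against.** The strongest case against has four parts.

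- **The coding is inferred.** Section 2.6.2 says only eGFR, and a condensed article may leave coding to a fuller document. This stands as a caveat. However, the term is listed as an allocation factor and section 2.4 defines that factor with two levels, so this is the natural reading of a model the article does specify.
- **Adjusting for stratification factors is a recognised, defensible choice.** This stands. Nothing in sections 2.4 to 2.6 is contradictory or invalid.
- **The gain is small.** This also stands: an SE of 0.406 against 0.399, with no change to the power claimed at the planned difference.
- **Added modelling can do harm.** Choosing a non-linear term or an interaction after looking at fit would be a data-dependent step in a confirmatory analysis. This stands too, and the functional form should be fixed in advance.

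A reader might infer more than the documents support:

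- **Baseline is the main driver of change.** The documents give no correlation, and under the assumptions above baseline explains about a tenth of the variance, much of it already taken up by the strata.
- **Single-reading selection biases the letter effect.** Regression to the mean acts equally in all randomised groups, so it does not. Chance imbalance is already reflected in the standard error.
- **Precision is critical because true differences must be well below 1 mL/min.** The only difference the article states is −3. Whether that target is realistic is a separate question, and this covariate would not settle it: at a true difference of 0.5, power moves only from about 23% to 24%.

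**Conclusion.** The point holds as a minor efficiency matter on a secondary outcome. On the natural reading of sections 2.4 and 2.6.2, a baseline with an SD of about 16 is reduced to one cut at 60, although the measured value must be available to compute the outcome. The comparison remains unbiased and the stated power of at least 99% at −3 remains correct.

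The loss is about 3.6% of residual variance at a slope of −0.2, and 0.9 to 9% (roughly 0.5 to 5% in SE) for slopes of −0.1 to −0.3. This rests on equal baseline and follow-up variances, a change SD of 10, and an assumed baseline distribution matched to Table 3. The selection simulation puts the SE gain toward the lower part of that range. If the eGFR term was in fact meant as continuous, the point reduces to stating the coding.

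**What to change.** In the linear model for eGFR change, pre-specify continuous pre-intervention eGFR (from the same checkup used to compute the change) as a covariate, alongside the group dummies, quarter, eGFR stratum and urine protein. State the coding of each term. Fix the functional form in advance, for example linear, with no terms added according to fit. Make the change before 2-year outcomes are examined.

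The cost is one line of wording and one model parameter. No additional data are needed, and neither the sample size nor the testing sequence changes.

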### Ethical statements

2.7

We are conducting the pragmatic RCT in cooperation with conventional health promotion activities by the health insurance association. In this study, we are using routinely collected data, not collecting additional data, to identify eligible participants, follow them, and assess their outcomes. The intervention just involves receiving letters to encourage patients to visit physicians without any obligation. Therefore, we received approval from the institutional review board of Kyoto University (approval number: C1420), and the need for informed consent from the participants was waived.

